Baseline/day 1	Informed e-consent procedure (link at bottom of this information page) Demographics questionnaire following consent page (~ 10 min) Email with a unique Participant ID (PID) and link to online platform for all further tasks and assessments. Baseline assessment (~ 30–40 min, must be on a computer) Email to inform you of allocation (*WoB or #Ash)	
Day 2	Morning mood (*WoB or #Ash) Evening Mood (~ 5 min, on device of choice)	
Day 3	Morning mood (*WoB or #Ash) Evening Mood (~ 5 min, on device of choice)	
Day 4	Morning mood (*WoB or #Ash) Evening Mood (~ 5 min, on device of choice)	
Day 5	Exit Assessment (~ 30-40 min, must be on a computer)	£30
6 weeks	Follow-up Assessment (~ 30-40 min, must be on a computer)	£10

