## Measures

### Primary outcomes

#### The Positive and Negative Affect Schedule

The Positive and Negative Affect Schedule (PANAS) is a widely used scale of emotion and comprises 20 items, 10 measuring positive affect (excited, inspired, etc.) and 10 measuring negative affect (upset, afraid, etc.), on a Likert Scale of 1 (very slightly) to 5 (extremely) [11]. This will be asked with reference to the previous seven days at baseline and 6-week follow-up, the previous 3 days at day 5 and at that precise moment twice daily during the 3-day intervention phase. The PANAS is a reliable and valid measure of depression and anxiety in young adults. The PANAS was chosen for this study as it is relatively stable but also sensitive to mood fluctuations if used with short-term instructions (e.g. now) [11]. The utility of this measure is enhanced by the provision of large-scale normative data in the general UK population [12]. The basic psychometric data for the PANAS was developed from studies in undergraduates, of a similar age range as the participants of this current study, and it is well validated in young adult populations [11].

In previous studies, negative and positive affect have emerged consistently as two dominant and relatively independent dimensions in the structure of affect. The Negative Affect (NA) scale of the PANAS is highly internally consistent, largely uncorrelated, and stable (Cronbach alpha reliabilities for intercorrelations and internal consistency range from .84 to .87) [11]. NA reflects the degree of subjective distress arising from various negative mood states, such as guilt, anger, fear and nervousness. High NA is related to self-reported stress and difficulty coping with negative events. The 10-item Positive Affect (PA) scale is valid and reliable with high internal consistency. Reliabilities range from .86 to .90 [11]. High PA is characterized by energy, concentration and engagement [11].

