### Power analysis and sample size

We aim to recruit over 400 participants. We approximated the statistical power to detect a significant effect of WoB on PANAS scores by assuming an effect size of 0.3 standard deviations of group (WoB vs. Ashmolean Website). With 200 participants in each group, and no pre-intervention differences, a Welch’s t test would have 85% probability of rejecting the null hypothesis under these parameters.

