### Analysis plan

A descriptive analysis will be performed for the whole population and each group (WoB and Ashmolean Website). Categorical variables will be described, presenting the numbers and frequency of each. Quantitative variables will be described using usual positional and dispersion parameters.

We will perform an intention to treat analysis to include all participants randomised with any outcome data. Participants will continue to be invited for assessments whether or not they use the allocated intervention. Missing item responses are not possible by design. Missing data, if any, will happen due to participants discontinuing with outcome assessments. However, their data for timepoints prior to that will still be included in the multilevel model, so no additional methodological steps are required regarding missing data.

For NA and PA we will separately regress the subscale means on baseline score (Day 1 measurement), an indicator for Group (Ashmolean website / WoB), and contrast code age (16-17 / 18-24), sex (Male / Female), ethnicity (White / Other), relationship status (In / Not in relationship or other), and current antidepressant use (Yes / No). We will include random intercepts for participants. As there are multiple timepoints at which the group comparison could be made, we will allow the Group effect to vary as a random effect across the measurement timepoints. We will perform a similar analysis for the K10, however as there are fewer measurement timepoints for the K10 compared to the PANAS (2 vs 8) we treat time points as fixed effects. This is the same for secondary outcomes, flourishing and loneliness. The 6-week measures are primarily included to assess whether early differences in the performance of cognitive tasks predict changes in the primary outcomes at 6 weeks.

We will conduct subgroup analyses based on age group (16-17 or 18-24), sex, ethnicity, baseline mental disorder, antidepressant use and previous regular use of online culture (more or less than once a month). We hypothesise that mental disorder at baseline, those not on antidepressants and regular users of culture would be more likely to demonstrate group differences.

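### The Day 2 morning PANAS precedes the first scheduled use of either website but is averaged into the primary Group effect, probably pulling it somewhat towards zero

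*Protocol article*

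**What the plan says.** Table 2 of the protocol article (under Participants and recruitment) closes Day 1, after the baseline assessment, with "Email to inform you of allocation (*WoB or #Ash". The rows for Days 2, 3 and 4 each read "Morning mood (*WoB or #Ash) Evening Mood (~ 5 min, on device of choice". The PANAS section places the momentary ratings "at that precise moment twice daily during the 3-day intervention phase" and the remaining ones "with reference to the previous seven days at baseline and 6-week follow-up, the previous 3 days at day 5".

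The Analysis plan will "regress the subscale means on baseline score (Day 1 measurement), an indicator for Group (Ashmolean website / WoB", plus further covariates and a random intercept per participant. On timepoints it says "we will allow the Group effect to vary as a random effect across the measurement timepoints". It treats time as fixed for the K10 because "there are fewer measurement timepoints for the K10 compared to the PANAS (2 vs 8". Nothing in the article removes the Day 2 morning rating from the outcomes or treats it as a pre-exposure reading.

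The sample size section supports 200 per group and 85% power by "assuming an effect size of 0.3 standard deviations of group (WoB vs. Ashmolean Website", using a Welch t test.

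**The concern.** A reading taken before scheduled exposure carries little information about what using the website does. When it is averaged with readings taken after use, it draws the estimate towards whatever the arms show beforehand, which with randomised groups is expected to be near zero. The random Group-by-timepoint term does not cure this. The reported Group effect remains a mean over all timepoints, and a reading that differs by design is modelled as one more draw from the distribution of real effects. That raises the estimated between-timepoint variance and hence the standard error.

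Both primary PANAS analyses, negative and positive affect, are affected. What is at stake is power, and whether the averaged effect answers the trial's question about using the website.

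**Working it through.** **1. Which readings make up the 8?** Momentary ratings: 3 days × 2 = 6. The other PANAS assessments are baseline, Day 5 and 6 weeks. The K10 is taken at baseline, Day 5 and 6 weeks. Candidate counts:

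| Reading of the count | K10 | PANAS | Fits 2 vs 8? | Day 2 morning in? |
|---|---|---|---|---|
| Post-baseline only | Day 5 + 6 weeks = 2 | 6 + 1 + 1 = 8 | yes | yes, 1 of 8 outcomes |
| Baseline counted, 6 weeks left out | baseline + Day 5 = 2 | 1 + 6 + 1 = 8 | yes | yes, 1 of 7 outcomes (baseline is a covariate) |
| Baseline counted, Day 2 morning dropped | 3 | 1 + 5 + 1 + 1 = 8 | no | no |

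The only count that drops Day 2 morning and still gives 8 contradicts the K10 figure. The Day 3 and Day 4 morning ratings follow earlier scheduled use and are properly post-exposure.

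**2. The protocol's own power figure.** Effect 0.30 SD, 200 per group, two-sided alpha 0.05 (assumed; the article states none). SE = √(2/200) = 0.10 SD, so effect/SE = 3.0. Power is 0.851 by the normal approximation and 0.849 by the noncentral t with 398 df. The stated 85% reproduces.

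**3. Upper size of the dilution.** Assume no effect at Day 2 morning, 0.30 SD at every other reading, and equal weights.
- 1 of 8: 0.30 × 7/8 = 0.2625 SD, which is 12.5% lower.
- 1 of 7: 0.30 × 6/7 = 0.257 SD, which is 14.3% lower.

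If part of the effect is already present at Day 2 morning (1 of 8):
- a quarter present: 0.30 × 7.25/8 = 0.272 SD
- half present: 0.30 × 7.5/8 = 0.281 SD

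**4. On the protocol's t-test scale, as illustration only.** At 0.2625 SD and 200 per group, power is 0.745 (t) or 0.747 (normal), and 261 per group would restore 85%. With a quarter or half of the effect already present, power is 0.776 or 0.803.

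**5. Closer to the planned model.** Let ρ be the within-person correlation between readings and r the correlation of baseline with each outcome, both assumed. The mean of k readings, adjusted for baseline, has variance v = (1 + (k − 1)ρ)/k − r² per person, and SE = √(2v/200). The single zero among eight gives a between-timepoint SD of 0.106, which adds 0.106/√8 = 0.0375 SD to the SE in quadrature. Power with the effects of step 3 (1 of 8):

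| r | ρ | Day 2 morning out (7 readings, 0.30) | In (8 readings, 0.2625) | In, with added between-timepoint variance |
|---|---|---|---|---|
| 0 | 0.5 | 0.978 | 0.938 | 0.879 |
| 0 | 0.7 | 0.936 | 0.864 | 0.800 |
| 0 | 0.9 | 0.881 | 0.785 | 0.725 |
| 0.3 | 0.5 | 0.991 | 0.968 | 0.918 |
| 0.3 | 0.7 | 0.960 | 0.904 | 0.841 |
| 0.3 | 0.9 | 0.911 | 0.825 | 0.763 |
| 0.5 | 0.5 | 1.000 | 0.997 | 0.974 |
| 0.5 | 0.7 | 0.990 | 0.964 | 0.912 |
| 0.5 | 0.9 | 0.957 | 0.897 | 0.834 |

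The last column applies the added variance only to the analysis that includes Day 2 morning, because a constant later effect is assumed. If the effect varies over time anyway, both analyses carry between-timepoint variance and the gap would differ. Under these assumptions inclusion loses power in every row, but the amount runs from under 1 point to about 16 points.

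**The case against.** - **Exposure.** A reader might infer that nobody can have used the website before the Day 2 morning rating. The article shows only that no use is scheduled earlier. Allocation is emailed on Day 1, no text bars an early look, and the table's footnotes for * and # and Fig. 2 are not shown. This stands: the point concerns scheduled use.
- **Zero effect.** Participants know their allocation, so expectancy could produce a difference by Day 2 morning. This stands too, which is why the percentages are upper sizes. The direction needs only a smaller effect at that reading than later.
- **Power.** A reader might infer that the trial's power falls from 85% to 74%, or that 261 per group are needed. Those figures apply an averaged effect to a single-measurement t test, and the sample size section does not tie its 0.3 SD to any timepoint. The plan is a baseline-adjusted repeated-measures model, and several rows of the last table exceed 85% with the rating included.
- **Intention to treat.** The rating is post-randomisation, so comparing arms on it is valid; averaging from allocation or from first scheduled use is partly a choice of estimand. That is fair, but intention to treat settles which people are analysed, not which readings count as outcomes. The stated objective is to compare the effectiveness of the two websites.
- **Random Group effect.** It allows for effects that differ by timepoint, so the 0.106 figure is specific to a constant later effect. It still does not take the reading out of the mean.

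**Conclusion.** The point holds as a design-of-analysis weakness of minor to moderate severity. By the schedule, Day 2 morning precedes first scheduled use in both arms, and under either count that fits the text it enters the averaged Group effect. The average is reduced by at most about 12.5% or 14.3% under the assumptions of step 3, and by less if expectancy or early use has already produced a difference. The rating also adds between-timepoint variation to the random Group effect.

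The bias is towards the null: it costs some power and interpretability and does not inflate type I error. A reader might infer that it invalidates the primary comparison. The article does not support that: the comparison remains randomised, the trial is described as exploratory, and one reading of seven or eight is concerned. The size of the power loss cannot be fixed from the article, because it gives neither the within-person nor the baseline correlation.

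**What to change.** State in the Analysis plan, before any unblinded analysis, that the primary PANAS Group effect for negative and positive affect uses ratings from Day 2 evening onward. The same sentence should list the outcome timepoints, so that it is clear whether the 6-week rating belongs to the set. Report Day 2 morning separately by arm, as a check on expectancy or early use, and add a sensitivity analysis that includes it in the average.

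The cost is a sentence or two and one extra model run per subscale. No assessment is added or dropped, since the rating is still collected. The downside is one fewer reading in the average, which slightly raises its sampling variance: at ρ = 0.7 without baseline adjustment, v goes from (1 + 7 × 0.7)/8 = 0.7375 to (1 + 6 × 0.7)/7 = 0.743. Fixing the rule in advance also keeps the exclusion from looking data-driven.

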### Embedded qualitative study

An embedded qualitative study will be conducted in order to ascertain participants experience of the interventions and research process to aid interpretation of the quantitative data and ascertain their views regarding the optimal use of the interventions and further testing. More specifically participants will be asked about the following:

Experience of the intervention
Helpfulness to mental healthAdverse or unintended consequencesOptimal time of useSuggestions for improvement for mental health

Experience of the research
How the process of participation in the study was experiencedHow the testing was experiencedSuggestions for improvement for the research process and/or testing

Participants who have consented for further contact will be selected purposively and iteratively. Baseline data will be used to ensure heterogeneity by sociodemographic characteristics, mental health status and previous use of online culture. Participants will be emailed to invite them to consent for a focus group. Focus groups will be conducted separately for each intervention arm at a time convenient to the participants via Zoom. These will be recorded and transcribed for analysis by a multidisciplinary team with expertise in qualitative methodologies. We aim for at least 12 participants to be included in focus groups. When assessing thematic saturation, the sample size will be reviewed [25].

At the 6-week follow-up, there will be free text items regarding what was positive about the research experience and what could be improved. There will also be items relating to the experience of using the allocated intervention and how its use could be optimised for mental health, including two free text options, ‘Please describe any noticeable positive or negative impacts of your allocated cultural experience’ and ‘Are there any ways in which the allocated intervention could be improved for mental health, in your opinion?’

Transcripts and free text responses will be analysed separately. Both transcripts and free text responses will be coded using specialist computer software, NVIVO [26]. Data analysis will take a sequential-explanatory approach [27]. We will combine deductive and inductive methods to investigate whether the theory developed in the preparatory phase holds true, but we will also be open to emerging themes. Analytic meetings will be held with the research team to discuss and optimise validity. Attention will be paid to integrating quantitative and qualitative aspects for evaluating the trial and its interventions [28].

### Monitoring

The study will be overseen by a Trial Steering Committee. The Trial Steering Committee will meet regularly and at key stages of the trial, at a minimum at planning, pre-recruitment and prior to completion. The Project Management group will meet at least weekly for the duration of the trial. Any data-related issues, should they arise will be discussed within the Project Management group and with the Trial Steering Committee at the next meeting, or meetings will be expedited if deemed necessary. Access to study data will be provided to authorised representatives from the Sponsor for monitoring and audit purposes if required.

The Trial Steering Committee consists of the Head of Department and researchers from the University of Oxford Department of Psychiatry, a Consultant Psychiatrist, two staff members from Oxford University Gardens, Libraries and Museums, three Public and Patient involvement (PPI) members, researchers from the Oxford Internet Institute (including the Director of Research) and three students and members of staff from the target age range. The Trial Steering Committee decided that a separate Data Monitoring Committee would not be necessary based on the short time frame of the intervention phase and low risk nature of the trial.

Both interventions and trial procedures relevant to the first 5 days of the study have already been trialled on eleven volunteers and detailed feedback taken and discussed in detail by the Trial Steering Committee. This is a low-risk study, and we do not anticipate any reasons for unblinding; therefore, study-specific interim analyses, stopping or unblinding procedures have not been put into place. Should the need arise, the relevant University of Oxford standard operating procedures will be followed.

## Discussion

O-ACE POP has two main goals. The first is to assess the effectiveness of a web-based cultural experience tailored to support mental health in young people compared with the Ashmolean Museum Website, on measures of mood, as well as loneliness and flourishing. The second is to investigate the impact on objective measures (cognitive tasks) predicting vulnerability to common mental disorders. Young people identified that human based narratives and other people’s viewpoints would have the potential to reduce distress, improve their mental health and enhance feelings of connection with others. This study will allow us to examine whether an intervention based directly on the opinions and experiences of young people and targeted at them has the potential to work over and above what is already available (without these specific features). This study will allow us to explore who, how and if online cultural experiences are effective for the mental health of young people.

Completing this study in this age range has many important advantages. First, given the trajectory of common mental disorders, this is a critical timepoint for minimising their impact in terms of disease burden, lifetime distress, illness and social and economic factors such as lost productivity. Second, this is a peak period for development of common mental disorders and, thus, a critical timepoint for prevention. Third, research in this age range is less likely to be confounded, for example by multiple episodes and medical or psychological interventions.

## Strengths

Many now advocate the engagement of young people, co-production and an increased evidence base for community interventions for CMDs in young people [5]. This trial is the first of its kind, and whilst ambitious in its endeavour, there are no previous trials of online museums for mental health in young people on which to build. We worked closely with young people of the target age-range to co-produce the web experience and with PPI of the target age range to design the experiment. We have kept broad inclusion criteria so as not to exclude people who could potentially benefit and use subgroup analyses to generate hypotheses as to the optimal use of these interventions, for investigation in further studies. We also piloted the study and intervention on eleven volunteers in order to assess smooth running of the procedures and identify any potential unintended or adverse effects. On detailed discussion amongst the study team and trial steering committee, given the feedback from volunteers, the nature of the interventions and length of the intervention phase, the risk of adverse effects were deemed minimal.

## Limitations

Due to technical aspects of the cognitive tasks and the WoB web-experience, for inclusion into this study participants require access to a computer (laptop or desktop) with a recent Web Browser. This may mean that some groups may not access this study or may not fulfil the inclusion criteria. It is difficult to assess how many people this may apply to. However, internet access in general has increased in recent years. In 2020, 96% of households in Great Britain had internet access, an increase from 93% in 2019 and 57% in 2006 [29]. Many of the barriers to internet use involve not wanting to use the internet or concerns regarding security [30]. It is not clear from the literature how many people in this specific age range would not have access to a computer with a recent browser and how this relates to their mental health need.

## Implications

Studies that attempt to quantify the potential benefits of community resources for mental health may aid policy makers to make informed decisions regarding allocation of limited resources. In addition, the accessibility of technological resources for using, optimising or testing the mental health benefits of community resources is a major consideration for which evidence is scarce. For example, further generations of optimised community webtool interventions and perhaps even the platforms for testing of their mental health benefits may become possible on Smartphones or Tablets, thus increasing the accessibility of such interventions and studies to people from lower income groups who may have reduced access and potentially greater mental health need. In addition, this study develops rigorous testing to methodologies which encompass engagement with young people and co-production of engaging and acceptable interventions.

The COVID-19 pandemic and associated restrictions has been detrimental to the mental health of the population but has provided a unique opportunity to design an innovative approach for mental health in young adults*.* Findings derived from this study will allow us to evaluate the efficacy of these interventions and will lay the groundwork for the design of studies to further enhance, refine and test online and in-person cultural resources for mental health in target populations. Moreover, it will allow us to identify whether online experimental studies in the area of community resources for mental health in young people are a fruitful avenue for research.

## Data Availability

The authors will have access to the study data. We plan to make the dataset and coding used for the analysis available on the Open Science Framework.
